### Study Overview

The Bread Related Effect on Microbial Distribution study was a double-blinded, placebo-controlled, crossover randomized controlled trial of healthy adults with low DF intake. The design and management of the clinical study adhered to the CONSORT (Consolidated Standards of Reporting Trials) guidelines [45]. This design accounts for the recognized variability in individuals and enables each participant to be their own control for their assigned interventions [46,47]. The study duration was a nominal total of 14 weeks, consisting of a 2-week lead-in phase, two 4-week intervention phases separated by a 2-week washout phase, and a final 2-week follow-up phase (Figure 1). During the first intervention period, one group of participants consumed 3 slices (for female individuals) or 4 slices (for male individuals) of DRB-fortified bread daily for 4 weeks, whereas the other group consumed placebo bread. Following a 2-week washout period, participants who consumed the fortified bread in the first period crossed over to consume placebo bread in the second period, and vice versa (Figure 2). Participants were instructed not to alter their diet during the 2-week washout period. The washout period was selected based on gut microbiota studies reporting a return of microbiota abundances to baseline level within 2 weeks after the intervention [48].

Before study commencement, a mutually agreed schedule was discussed and set with each participant to ensure that they understood all expected clinic or visit times and the study timeline. However, when a participant could not come to the clinic on the day a phase was ending, the participant’s needs were accommodated by allowing for earlier visits to the clinic for up to 3 days before the end of the intervention phase (minimum of 25 days of the 28-day intervention). This approach reduced the risk of participants exhausting intervention supplies before the visit and noncompliance or dropout due to scheduling issues.

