### Randomization

One week before the first baseline visit, participants were randomly assigned in a 1:1 allocation using randomized permuted blocks (block size 4) to either DRB-fortified or placebo bread. Randomization was performed by drawing a folded note from a sealed opaque box.

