Differential relative abundance was performed using *DESeq2* in R (version 1.40.2; R Foundation for Statistical Computing). This package analyzes differential expressed taxa based on a negative binomial distribution. The effect of group was assessed by comparing between groups. The top 10 differentially abundant taxa were extracted based on adjusted *P* values for both baseline and postintervention assessments for each group. Taxa that changed within each group were identified by finding the set difference between the top taxa between baseline and the postintervention assessment. Log2FoldChange values were extracted for the identified changed taxa in each group [64]. Enrichment of functional gene attributes arranged hierarchically as level 1 (broadest level of function, eg, metabolism and cellular processes), level 2 (specific functions, eg, carbohydrate metabolism and amino acid metabolism), and level 3 (detailed pathways, eg, glycolysis and glycan degradation) were analyzed using the R package *Microbiome Multivariable Associations with Linear Models*, which uses general linear models that accommodate crossover designs [65]. Fixed effects included in the model were groups (DRB-fortified vs placebo bread).

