#### Sample Size

Sample size calculations were based on the GutFeelingKB cohort [92]. The percentage of relative abundance of a composite microbiome index (incorporating 15 operational taxonomic units as outlined in this section) was estimated to be 28.3% with an SD of 14%. The sample size needed was 60 participants in this crossover study to account for a 15% dropout rate. The crossover study had >80% power to detect a difference in the absolute increase in the relative abundance of approximately 6% as statistically significant (2-tailed α=.05). An increase of 6% compared with the baseline level of 28% equates to a relative increase of approximately 22%. The consumption of 3 (for female individuals) or 4 (for male individuals) slices of DRB-fortified bread per day for 28 days is thought to affect individual and combined groups of the microbial taxa making up the composite.

The composite microbiome index included genera from 5 phyla found in the gut microbiota of healthy human adults. This index included the *Prevotella* and *Barnesiella* genera and *Bacteroides ovatus* and *Bacteroides xylanisolvens* from the *Bacteriodetes* phylum; the *Roseburia*, *Anaerostipes*, *Blautia*, *Eubacterium*, *Ruminococcus*, *Faecalibacterium*, and *Lactobacillus* genera from the *Firmicutes* (*Bacillota*) phylum; the *Bifidobacterium* and *Eggerthella *genera from the *Actinobacteria* (*Actinomycetota*) phylum; the *Akkermansia* genera from the *Verrucomicrobiota* phylum; and the *Methanobrevibacter* genera from the *Euryarcheaota* phylum.

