#### Statistical Analysis Plan

This study was conducted as a superiority trial. The guidelines of the Committee for Proprietary Medicinal Products (now termed Committee for Medicinal Products for Human Use) require intention-to-treat analysis [93]. For a crossover design, the intention-to-treat analysis means that every enrolled participant who has consumed both the intervention and placebo bread is included despite dropout or noncompliance. All data from randomized participants who received at least one intervention dose and had at least one postintervention measurement will be analyzed.

The mean differences from the baseline of most outcomes will be compared between groups and referred to as a between-group comparison. For most outcomes, within-group analysis (after the intervention compared with baseline) will also be performed. For metabolome analyses, postintervention values (not the mean differences) will be compared within and between groups.

All statistical analyses will be performed using SPSS statistics (version 29; IBM Corp) or R (version 4.3.1) by blinded researchers under the guidance of an independent biostatistician.

Baseline characteristics will be presented using descriptive statistics. The mean and SD, or median and range, will be used to describe continuous variables. Frequencies or percentages will be used to describe categorical variables. The group effects (ie, the mean change from baseline between groups) will be assessed using (parametric) 2-tailed *t* tests and (nonparametric) Mann-Whitney or Kruskal-Wallis tests for symmetrically and asymmetrically distributed data. Categorical variables will be assessed using chi-square tests (or Fisher exact tests for small samples). A 2-tailed *P*<.05 is determined as statistically significant. A value of *P*≤.10 will be considered a trend for most variables except for the microbiome data.

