For the primary outcome, to determine the microbiome composite, the selected genera and species will be summed to give a composite relative abundance for each participant. Changes in the composite of the microbial taxa within and between groups will be assessed using the nonparametric Wilcoxon signed rank test. The statistical significance level is determined at *P*<.05, with a false discovery rate (FDR) of *P*<.10. A probable biological significance level (trend) is assumed at an unadjusted *P*≤.10. For other fecal microbiome measures, univariate and multivariate statistical analyses will be used to assess α- and β-diversity variations, individual relative abundance differences in taxa, and gene abundance differences between groups. Differences in α-diversity between baseline and the postintervention assessment and between groups after the intervention will be assessed using the nonparametric Wilcoxon signed rank test with continuity correction. The Benjamini-Hochberg method will be applied to control the FDR inherent in multiple-hypothesis testing for variables in the microbiome and metabolome analyses. The resulting adjusted *P* values will be computed to address the inflated type-I error rates associated with numerous comparisons. *P*<.05 and an FDR of *P*<.10 will be deemed significant, with a probable biological significant difference (trend) assumed at an unadjusted *P*≤.10.

Box plots will be created using *ggplot2* to compare groups for each Chao1 and Shannon Indexes. The permutational multivariate ANOVA and the analysis of dissimilarity functions will then be used to assess the statistical significance of microbial community composition between individuals. Analysis of dissimilarity uses permutation testing and provides statistical assessments and their significance using *F* tests based on the sequential sums of squares from the permutations to determine whether the observed differences in β-diversity are statistically meaningful. Microbial differential gene expression will be performed using quasi-likelihood *F* tests. This test provides stricter error rate control by accounting for the uncertainty in dispersion estimation. Genes with an absolute log fold change of >1.1 will be considered as differentially expressed.

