As mentioned previously, the comparisons will be between each group and baseline and between groups after the intervention for plasma or fecal metabolome measures. The partial least squares projection discriminant analysis (PLS-DA) model will be performed to identify metabolites using SIMCA (version 17; Umetrics). The PLS-DA models will be subject to 100-fold permutations to evaluate performance; the models will be validated using the predictive ability of the model (Q2) and the ANOVA testing of cross-validated predictive residuals (ANOVA testing of cross-validated predictive residuals) [94]. The most discriminating features will be selected for building PLS-DA models. These models will be again subjected to prediction accuracy and overfitting assessment by the corresponding tests (ANOVA testing of cross-validated predictive residuals) and comparison of the Q2 afterward. Features will be selected based on their variable importance in the projection score. Univariate statistical analysis and heat maps will be performed using MetaboAnalyst (version 5.0) [95]. The metabolite and lipid relative intensity differences between groups will be tested through *t* tests or Wilcoxon rank sum tests. The multiple testing corrections will be controlled using FDR correction [96].

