Fecal samples were collected to determine the gut microbiota composition, gene abundances, bile acid concentrations, organic acid concentrations, and moisture content. Immediate analysis of fresh fecal samples is often unrealistic, raising concerns about storage methods by participants, which may cause microbial DNA degradation, overgrowth, and species death in fecal samples [97]. However, there are room-temperature microbial stabilization methods with high technical reproducibility and compositional stability [98], which should be considered for future studies. From a cultural perspective, these advanced methods offer an alternative for future studies in which refrigerating fecal samples is not feasible, particularly in cases in which it may be culturally insensitive, such as for Māori and Pasifika participants. Nonetheless, all participants were given clear written instructions, ice packs, and a cooler bag for returning their samples during clinic visits, minimizing potential confounding effects.

Strengths of the Bread Related Effect on Microbial Distribution study include using shotgun metagenomics to analyze extracted fecal microbial DNA. This approach allowed for the exploration of the composition and predictive functional aspects of the gut microbiota. These analyses provided insights into the community structure and diversity as well as the identification of changes in taxa and genes associated with the study interventions [99]. In addition, this study included other multiomic approaches (metabolomics), validated subjective questionnaires, and dietary records collected before and after each intervention. Integrating these data will allow for a better understanding of the complex interactions among diet, gut microbiota, and other health outcomes in healthy adults with low DF intake. Furthermore, this study is a blinded crossover study, allowing participants to be their own controls [47]. A crossover design was chosen due to the recognized inter- and intraindividual variabilities among populations, allowing for a reduced sample size while achieving the required statistical power. In addition, sequence effects were accounted for in the analysis [100].

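### Comparisons between breads for secondary and metabolome outcomes are assigned independent-sample tests although the same participants eat both breads, and no listed analysis makes the sequence adjustment that the Discussion reports

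*Protocol article*

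**What the plan says.** - **Design.** The Study Overview says the crossover "enables each participant to be their own control for their assigned interventions". The Discussion gives the smaller sample size as a reason for choosing it.
- **Most outcomes.** The Statistical Analysis Plan section compares changes from baseline between groups, and the Abstract shows that the groups are the two breads. It names two-tailed t tests, without saying whether they are paired, and "nonparametric) Mann-Whitney or Kruskal-Wallis tests for symmetrically and asymmetrically distributed data". Categorical variables get chi-square tests, or Fisher exact tests in small samples.
- **Metabolome.** Postintervention values, not changes, are compared, using t "tests or Wilcoxon rank sum tests".
- **Primary composite.** "Changes in the composite of the microbial taxa within and between groups will be assessed using the nonparametric Wilcoxon signed rank test". Alpha-diversity is also given the signed rank test.
- **Functional gene model.** The Microbial Composition and Gene Abundances section says the modelling package can handle crossover designs. It then states: "Fixed effects included in the model were groups (DRB-fortified vs placebo bread)".
- **Sequence.** The Discussion, under Anticipated Findings, says that "sequence effects were accounted for in the analysis".

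**The concern.** Mann-Whitney, Kruskal-Wallis, rank sum, chi-square and Fisher exact tests all assume that the compared samples come from different people. Here they come from the same people. If a participant's two values are positively correlated, an independent-sample test uses too large a standard error and loses the within-person gain for which the crossover was chosen. If they are negatively correlated, the standard error is too small and the test gives too many false positives.

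This does not look like loose terminology, because the same section names the signed rank test for the composite and the rank sum test for metabolites. It is a stated choice of method, not a detail left to a fuller plan.

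At stake are the secondary families: gut comfort, well-being, diet, lipids, transit time and metabolites. For metabolites, an overly conservative test is followed by a false discovery rate correction, so real effects could be missed twice over.

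The sequence statement is a separate problem. A reader of the Discussion would believe that an adjustment had been made, but the listed analyses contain none.

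**Working it through.** **1. The plan's own figure.** The Sample Size section gives a 6-point difference, an SD of 14, two-sided alpha 0.05, 60 participants and 15% dropout ("The sample size needed was 60 participants in this crossover study to account for a 15% dropout rate"), so 60 × 0.85 = 51 completers. It claims more than 80% power.

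- Paired, with 14 taken as the SD of the within-person difference: 6 × √51 / 14 = 3.06, and Φ(3.06 − 1.96) = 86% (85% with the noncentral t). The claim reproduces.
- Two independent groups of 51 with SD 14: 6 / (14 × √(2/51)) = 2.16, and Φ(2.16 − 1.96) = 58%.

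The stated power therefore fits a paired analysis. The article does not say which SD the 14 is. If it is the SD of a single value, the paired reading corresponds to a within-person correlation of 0.5.

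**2. Independent-sample test on paired data.** Let n = 56 (the analysed number in Results), with each value having SD 1. Let ρ be the correlation between a participant's two values. The article does not give ρ, so a range is shown.

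- Standard error the test assumes: √(2/56) = 0.189.
- True standard error: √(2(1 − ρ)/56).
- Critical difference: 1.982 × 0.189 = 0.3745 (t with 110 df).
- Type I error: 2 × [1 − Φ(0.3745 / true SE)].
- Power at 0.4 SD: about Φ((0.4 − 0.3745) / true SE).
- Paired power: noncentral t with SD of difference √(2(1 − ρ)).

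Metabolome (raw postintervention values, where the participant's own level stays in the data):

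| ρ | True SE | Type I error, independent test | Power, independent test | Power, paired test |
|---|---|---|---|---|
| 0.5 | 0.134 | 0.5% | 58% | 84% |
| 0.7 | 0.104 | below 0.1% | 60% | 97% |

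Change scores (most other outcomes, where each period's own baseline removes much of the participant's level):

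| ρ between the two changes | True SE | Type I error, independent test |
|---|---|---|
| +0.25 | 0.164 | 2.2% |
| 0 | 0.189 | 4.8% (nominal, within the approximation) |
| −0.25 | 0.211 | 7.6% |

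**3. Check on the rank tests themselves.** A simulation with 20,000 replicates of 56 normal pairs and a true difference of 6/14 SD gave:

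| ρ | Mann-Whitney: type I error, power | Signed rank: type I error, power |
|---|---|---|
| 0 | 0.050, 60% | 0.049, 59% |
| 0.25 | 0.026, 60% | 0.053, 71% |
| 0.5 | 0.007, 62% | 0.048, 86% |
| −0.3 | 0.082, 58% | 0.049, 48% |

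The rank tests behave as the t-based formula predicts.

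**4. The sequence statement against the listed methods.** The signed rank test has no period or sequence term. The t, Mann-Whitney, Kruskal-Wallis, rank sum, chi-square and Fisher tests as listed have none either. The gene model has one stated fixed effect, bread. So nothing listed produces the adjustment that the Discussion reports.

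**5. What an omitted period effect could do to a paired test.** This was simulated at ρ = 0.5, with an assumed period effect of 0.5 SD in the analysed quantity. With sequences of 28 and 28 there is no bias; type I error is 0.028 and power 83%, against about 0.05 and 88% with period adjustment. With 32 and 24 the estimate shifts by 0.5 × 8/56 = 0.07 SD. The article does not give the actual split.

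**The case against.** Several points on the other side stand.

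- **Primary outcome.** A reader might infer that the trial's main P value is wrong. The documents do not support that: the composite and alpha-diversity are assigned the paired signed rank test. The independence error is confined to the other outcomes.
- **t tests.** They are not stated to be unpaired. The point rests on the named rank and categorical tests, and for the t tests it is only an ambiguity.
- **Change scores.** Subtracting each period's baseline may bring the correlation near zero, where the independent-sample tests are about right. The large power losses apply to raw metabolome values at an assumed correlation and should not be read across to every outcome.
- **Gene model and beta-diversity.** A reader might infer that the gene model ignores participants. The article says the package accommodates crossover designs, and a list of fixed effects does not say whether a participant random effect was fitted. No permutation scheme is stated for beta-diversity, so silence there shows no error.
- **Period bias.** A reader might infer that dropout has biased the bread contrast. If 31 were randomized to each sequence (an assumption) and all 6 dropouts came from one, 6/56 = 11% of any period effect would leak into it. That is a worst case: if dropout is unrelated to sequence, its probability is 2 × C(31,6)/C(62,6) = 2.4%. A period shift common to baseline and postintervention also cancels in a change score, and the article gives no evidence of a period effect.
- **Sequence statement.** It cites a source not shown here, and model terms are often left to a fuller plan. That would excuse silence. But the article lists its tests and model terms and separately asserts an adjustment that none of them makes, so the passages still need reconciling.

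**Conclusion.** The point holds for secondary and metabolome outcomes. The named rank and categorical tests are the wrong kind for two measurements on the same people.

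The size depends on a within-person correlation that the article does not give. For raw metabolome values at an assumed 0.5, with 56 people and a 0.4 SD effect, power falls from 84% to about 58% and true type I error is about 0.5%. For change scores, type I error ranges from about 2.2% to 7.6% over correlations of +0.25 to −0.25 and is close to nominal at zero. At positive correlation the harm is missed effects; at negative correlation it is false positives.

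The primary signed rank analysis does not have this error. Its lack of a period term is a reason for a sensitivity analysis, not a ground for calling it invalid.

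The Discussion's sequence statement is unsupported by any analysis that the article lists.

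**What to change.** 1. **Secondary and metabolome outcomes.** In the Statistical Analysis Plan section, replace the independent-sample tests with a crossover analysis: a mixed model with bread, period and sequence as fixed effects and participant as random effect.
2. **Skewed outcomes.** Use a rank sum test between the two sequences on within-person period differences, which allows for period, or a signed rank test between breads.
3. **Binary outcomes.** Use McNemar or conditional logistic regression.
4. **t tests.** Wherever one is kept, say that it is paired.
5. **Sequence.** Include period and sequence in these models and in the functional gene model, and state how participant is handled in the latter. The Methods will then agree with the Discussion.
6. **Primary outcome.** Keep the signed rank test as primary and add a period-adjusted analysis of the composite as a sensitivity analysis. Report the number analysed in each sequence.

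The cost is analysis wording, code, and one or two degrees of freedom per model. No new data are needed. Recruitment is complete, so the change should be dated and documented.

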### Hypotheses and Objectives

This study was based on the hypothesis that the consumption of 3 (for female individuals) or 4 (for male individuals) slices of DRB-fortified bread per day for 4 weeks will increase the relative abundance of a composite of key genera and species in fecal samples (proxy of lower gut microbiota) known to be involved in plant glycan metabolism or known to be modulated by the DRB-fortified bread.

Secondary hypotheses were that consumption of DRB-fortified bread would lead to improvements in clinical, patient-reported outcomes; biological measurements; whole-gut and regional transit time; and gas fermentation profiles.

DFs are compounds that require a network of microbes to degrade their complex structures [42,43]. Furthermore, due to the inconsistent findings on the relative abundance of microbial taxa reported by existing rice bran studies, a microbiome composite index is a useful primary outcome for this study.

The primary aim of this study is to determine the influence of the consumption of 3 (for female individuals) or 4 (for male individuals) slices of DRB-fortified bread on the composition of selected genera and species of microbiota that are known to be involved in plant glycan metabolism or known to be modulated by DRB-fortified bread using shotgun metagenomics sequencing of fecal samples.

The secondary aims were to investigate the influence of the consumption of 3 (for female individuals) or 4 (for male individuals) slices of DRB-fortified bread in comparison with placebo white bread on (1) upper- and lower-gut comfort using validated gut-specific questionnaires; (2) mental health and general well-being parameters using validated questionnaires; (3) DF intake using 3-day food diaries; (4) relative abundance of individual taxa, predictive function (gene abundances), and diversity indexes of the fecal gut microbiota using shotgun metagenomic sequencing and of fecal and plasma metabolites using liquid chromatography mass spectrometry (LCMS); (5) cardiovascular risk profile based on anthropometry, blood pressure, and blood lipid concentrations; (6) whole-gut transit time using blue food dye in all participants; and (7) regional and whole-gut transit time and gas fermentation profiles using Atmo gas capsules (Atmo Biosciences) in a subset of participants.

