#### Biological Measurements

##### Fecal Samples

###### Overview

The primary outcome was the differences in the relative abundance of a composite of selected key genera and species of the gut microbiota known to be involved in plant glycan metabolism or known to be modulated by the DRB-fortified bread (see the *Sample Size* section for more details) as compared with the placebo bread.

Once enrolled, participants received a posted cooler bag containing a fecal collection kit and ice pack. Participants collected a fecal sample into the provided fecal container 24 hours before their clinic visits at baseline, the postintervention time point of each phase, and follow-up. Participants were instructed to label the fecal container with the time and date collected and record it again on the bowel movement diary app. Participants had to refrigerate the collected fecal sample and transport it within 24 hours of sample collection in the provided cooler bag for each clinic visit. If participants could not provide a fecal sample 24 hours before, they were encouraged to collect and bring the sample in the cooler bag as soon as possible following their clinic visits.

In total, 5 aliquots (1 g each) of a fecal sample were frozen for microbial composition, gene abundance, and metabolite analyses. The samples were kept chilled until aliquoted in the laboratory. All aliquots were snap frozen in liquid nitrogen before storage at –80 °C until analysis.

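### The primary composite carries an unadjusted P≤.10 trend level that the same section rules out for microbiome data, and no deciding test is named among its within-bread and between-bread comparisons

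*Protocol article*

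**What the plan says.** All references are to the protocol article.

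- **General rule (Statistical Analysis Plan, paragraph on descriptive statistics and tests).** Two-tailed P<.05 is significant. P≤.10 "will be considered a trend for most variables except for the microbiome data".
- **Primary outcome (Statistical Analysis Plan, paragraph on the composite).** "Changes in the composite of the microbial taxa within and between groups will be assessed using the nonparametric Wilcoxon signed rank test". Significance is P<.05 with a false discovery rate (FDR) below .10. Then: "A probable biological significance level (trend) is assumed at an unadjusted" P≤.10.
- **Other microbiome measures (same paragraph).** The same pair of levels is repeated, "with a probable biological significant difference (trend) assumed at an unadjusted" P≤.10.
- **Primary hypothesis (Hypotheses and Objectives).** Three or four "slices of DRB-fortified bread per day for 4 weeks will increase the relative abundance of a composite of key genera and species". No comparator is given. The primary aim in that section has none either, while the secondary aims there are set against placebo white bread.
- **Outcome definition (the Overview part of Fecal Samples).** The article puts it thus: "The primary outcome was the differences in the relative abundance of a composite of selected key genera and species of the gut microbiota", with placebo bread as the comparator. Anticipated Findings also states the primary aim against placebo bread.
- **Sample Size.** Above 80% power for a difference of about 6 percentage points at a two-tailed α of .05.

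**The concern.** Two statements about the same data disagree. One says P≤.10 is not a trend for microbiome data. The other applies that cut-off, without adjustment, to the primary composite, which is microbiome data, and gives it the stronger label of probable biological significance.

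The primary-outcome paragraph also puts the change on DRB bread, the change on placebo bread and the difference between breads on the same footing. Because the hypothesis names no comparator, a before-after rise on DRB bread satisfies its literal wording. Such a rise could come from time, season or eating three to four slices a day of any bread. The placebo phase exists to remove those explanations. A report written to the letter of this paragraph could therefore present a within-bread rise, or a result between .05 and .10, as support for the primary hypothesis.

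**Working it through.** **1. The plan's own figure.** Inputs from Sample Size: 60 enrolled, 15% dropout, difference 6, SD 14, two-tailed α .05. Evaluable n = 60 × 0.85 = 51. Take 14 as the SD of the within-person difference (an assumption; it equals a within-person correlation of 0.5 if 14 is the between-person SD).

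- 6 / (14/√51) = 3.06, and 3.06 − 1.96 = 1.10, so power is 86% (85% with the noncentral t).
- The claim of more than 80% holds for one two-sided test at .05. It needs a correlation of at least about 0.40.

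**2. Error if either of two tests could carry the claim.** Let a and b be the standardised mean changes on DRB and placebo bread. With no effects and independent changes (assumed), the between-bread statistic is c = (a − b)/√2. It correlates 1/√2 ≈ 0.71 with a, so the tests overlap. Simulated rates:

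| Rule | P<.05 | P<.05 and Benjamini-Hochberg <.10 over three tests | P≤.10 |
|---|---|---|---|
| One between-bread test, two-sided | 5% | – | 10% |
| Within-DRB or between, two-sided | 8.3% | 6.5% | 16% |
| Within-DRB or between, favourable direction only | 4.1% | 3.2% | 8% |
| Any of the three, two-sided | 11.5% | 8.5% | 21.5% |

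The favourable-only row is the one to compare with a superiority claim. One two-sided test at .05 has 2.5% in that direction, and one at .10 has 5%. Two non-overlapping tails would give 2 × 2.5% = 5.0%; the overlap removes about 0.9 points, leaving 4.1%.

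Sensitivity: if the two changes correlate 0.3 to 0.5, the two-sided within-DRB-or-between rate is 8.8% to 9.1% at .05 and 17.0% to 17.5% at .10. With Wilcoxon signed rank tests at n=56 and correlation 0 or 0.3, it is 8.4% to 8.6% at .05.

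The FDR family for the composite is not stated, so three tests is an assumption. If the family is the single between-bread contrast, the FDR condition is P<.10, which P<.05 already implies, and it does nothing.

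**3. A shift shared by both breads, with no bread effect.** One-sample t test on the DRB change, n = 56 (the number analysed, from Results), noncentrality = d√56, where d is the shared shift in SDs of change. The documents give no value for d.

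| d (assumed) | d√56 | Within-DRB P<.05 |
|---|---|---|
| 0.1 | 0.75 | 11% |
| 0.2 | 1.50 | 31% |
| 0.3 | 2.24 | 60% |

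By Wilcoxon, the 0.2 and 0.3 rows give about 30% and 58%. The shared shift cancels in the between-bread contrast, which stays at 5%.

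**The case against.** The comparator is not in doubt across the article as a whole. The outcome definition and Anticipated Findings both name placebo, the trial is declared a superiority trial, and Sample Size sets one α of .05. Within-group analysis is introduced in the general text as an addition. A reader might infer that the plan lets a within-DRB rise alone count as a positive primary result; no sentence says so, and these sections point the other way. This part of the objection stands.

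A reader might also infer that the primary claim runs at more than 5% error. That does not follow. P≤.10 is called a trend, kept apart from statistical significance. The 8.3% and 11.5% figures count both directions and leave out the FDR condition, and the any-of-three figure includes changes on placebo bread alone, which nobody would read as success for DRB. In the favourable direction the rate at the significance level is 4.1% or 3.2%: above 2.5%, but not above 5%.

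Finally, the exemption can be read softly: microbiome data are left out of the general rule because the next paragraph gives them their own. This only partly helps. The specific rule has the same .10 cut-off, is expressly unadjusted and carries a stronger name, so the exemption would exempt nothing.

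**Conclusion.** The concern holds as a conflict in stated rules, and it should be fixed. The two paragraphs of the Statistical Analysis Plan section cannot both stand on the .10 level for microbiome data. The primary-outcome paragraph also lists several comparisons without naming the one that decides.

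The size depends on how the paragraph is used. If the between-bread contrast alone decides at P<.05, the error is the planned 5% two-sided. If a within-DRB rise could also support the claim, favourable-direction error goes from 2.5% to about 4.1% (3.2% with the assumed three-test FDR family), and to about 8% for the trend label. These figures assume no effects and independent changes. The more serious exposure is bias from a shared shift, 11% to 60% over the assumed range of 0.1 to 0.3 SD; the documents do not say how large such a shift would be.

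Nothing here undermines the design or the stated power for the placebo contrast.

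**What to change.** - In the primary-outcome paragraph, name the DRB-minus-placebo contrast on the composite, two-sided P<.05, as the only confirmatory test.
- Report the change on each bread as an estimate with an interval, without a significance claim.
- Delete the P≤.10 level for the primary outcome and the other microbiome measures, so that both paragraphs agree.
- Keep the FDR for the taxon, gene and metabolite families, where there are many tests.
- Add placebo bread as the comparator in the primary hypothesis.

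The cost is wording only: no new data and no change to sample size. The investigators give up labelling results with .05<P≤.10 as a probable biological effect.
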